# Effects of improved information and volunteer support on segregation of solid waste at the household level in urban settings in Madhya Pradesh, India (I-MISS): protocol of a cluster randomized controlled trial

**DOI:** 10.1186/s12889-021-10693-0

**Published:** 2021-04-09

**Keywords:** Urban, Household waste segregation, Randomised controlled trials, Solid waste management, Protocol, India

## Abstract

**Background:**

Segregation of household waste at the source is an effective and sustainable strategy for management of municipal waste. However, household segregation levels remain insufficient as waste management approaches are mostly top down and lack local support. The realisation and recognition of effective, improved and adequate waste management may be one of the vital drivers for attaining environmental protection and improved health and well-being. The presence of a local level motivator may promote household waste segregation and ultimately pro-environmental behaviour. The present cluster randomized control trial aims to understand if volunteer based information on waste segregation (I-MISS) can effectively promote increased waste segregation practices at the household level when compared with existing routine waste segregation information in an urban Indian setting.

**Methods:**

This paper describes the protocol of an 18 month two-group parallel,cluster randomised controlled trialin the urban setting of Ujjain, Madhya Pradesh, India. Randomization will be conducted at ward level, which is the last administrative unit of the municipality. The study will recruit 425 households in intervention and control groups. Assessments will be performed at baseline (0 months), midline (6 months), end line (12 months) and post intervention (18 months). The primary outcome will be the comparison of change in proportion of households practicing waste segregation and change in proportion of mis-sorted waste across the study period between the intervention and control groups as assessed by pick analysis. Intention to treat analysis will be conducted. Written informed consent will be obtained from all participants.

**Discussion:**

The present study is designed to study whether an external motivator, a volunteer selected from the participating community and empowered with adequate training, could disseminate waste segregation information to their community, thus promoting household waste segregation and ultimately pro-environmental behaviour. The study envisages that the volunteers could link waste management service providers and the community, give a local perspective to waste management, and help to change community habits through information, constant communication and feedback.

**Trial registration:**

The study is registered prospectively with Indian Council of Medical Research- Clinical Trial Registry of India (CTRI/2020/03/024278).

## Background

Globally, solid waste management is a major environmental issue. As of 2016, annual global Municipal Solid Waste (MSW) generation levels are 2.01 billion metric tonnes (MTs), with the per capita waste generation of 740 g per day. Owing to rapid urbanization and population growth, waste generation is expected to increase by 70% from 2016 levels to 3.4 billion MTs per year in 2050 [1, 2]. Proper segregation and disposal of generated waste is one of the important challenges being faced globally for attaining environmental protection and improved health and well-being [3–5]. Low- and middle-income countries (LMICs) specifically face continuous challenges in providing sustainable waste management services to their population due to the lack of organisation, financial resources, and the systems’ complexity [4, 6–8]. The importance of solid waste management has been recognized and embedded in all the Sustainable Development Goals (SDGs) either directly or indirectly. Hence, progress in solid waste management is important to deliver almost all of the SDGs [9].

India, the second populous country in the world, generates 147.6 million metric tonnessolid waste per day. The per capita waste generation ranges from 170 g to 620 g per day with an annual increase of 1.3% [2]. Recently the Government of India developed strategic plans, updated regulatory frameworks for solid waste management and started many initiatives to achieve sustainable waste management systems for Indian cities [10]. Despite these efforts, the progress in solid waste management in India has been slow. One of the factors responsible for the slow progressis the ‘top-down approach’ [10, 11]. Constitutionally, solid waste management comes under the purview of Urban Local Bodies (ULBs) [12]. However, in reality community participation in the process of solid waste management is often neglected [10, 12]. Further, there is limited environmental awareness among the public resulting in public attitudes creating barriers to improving waste management [13].

Studies have shown that empowering the community by providing appropriate knowledge and motivation, with an enabling environment and involving the community in waste management processes result in improved waste management practices at the household level, for example increased waste segregation and recycling behaviour [14, 15]. However, studies have also identified that sustaining the changed behaviour is the biggest challenge [16]. An external motivator and/or a local volunteer could promote sustainable change in household waste segregation practices and ultimately pro-environmental behaviour [17–20]. The volunteers could act as a link between the waste management services and the community, give a local perspective to waste management, and help change community habits through information, and constant communication and feedback, thus addressing many of the identified barriers. Volunteer-based interventions can also help in identifying other, contextually appropriate, ways of waste management [21, 22]. To our knowledge there are no such interventions reported in Indian context.

Therefore we propose the study to measure the impact of volunteer based one-on-one delivery of improved waste segregation information at household level. As the intervention is at household level and targeting behaviour change at household level as an outcome, we chose to adopt a cluster-randomized controlled trial (c-RCT) design to reduce the risk of potential contamination.

This paper describes the study protocol of an 18 month two-group parallel, c-RCT that aims to examine the effects of improved information and volunteer support on waste segregation at the household level in urban settings of Ujjain in Madhya Pradesh, Central India.

## Methods

### Hypothesis

We hypothesize that in urban settings of Central India, a volunteer based delivery of improved information on waste segregation (I-MISS) fortnightly for 12 months at household level in addition to the routine/ general information on waste segregation given by the municipality, will improve household waste segregation practices when compared to the households receiving only routine/general information on waste segregation given by the municipality.

### Objective

To examine the effects of improved information and volunteer support on waste segregation practices at the household level in urban settings of Ujjain in Madhya Pradesh, India.

### Study design

This is an 18 month two-group parallel, c-RCT. The trial will be conducted following the Consolidated Standards of Reporting Trials (CONSORT)- extension for c-RCT guidelines [23]. The protocol is prepared in agreement with the standard protocol Items from the recommendations for interventional trials (SPIRIT) guidelines [24]. In our study, we will randomize at ward level i.e., wards will be our cluster randomization unit. Wards are the last administrative unit of municipality. The wards will be stratified into four stratum based on the percentage of slum population within a ward. From each stratum, wards will be randomized into intervention and control arms with 1:1 allocation ratio. The study design and trial flow are depicted in Fig. 1.

**Fig. 1 Fig1:**
[figure not shown]
Design and participants flow chart according to SPIRIT 2013 guidlines (Standard protocol items: Recommendations for International Trials)

### Study setting

This study will be conducted within the area of the Ujjain Municipal Corporation in Madhya Pradesh, Central India. Ujjain city is a medium sized city in India with a municipal area of 93 sq. km. The population is 0.56 million and the slum population is around 23.32% of the total population [25, 26]. The Ujjain Municipal Corporation area is comprised of six zones and 54 administrative wards [25]. Nearly 225 MTs of total municipal solid waste is generated in Ujjain City daily [27].

### Study Population

Households located within the administrative boundary of Ujjain Municipal Corporation will be our study population.

#### Inclusion criteria

We will include households with at least one member above 18 years of age located within the administrative boundary of Ujjain Municipal Corporation with domiciliary stability of about 2 years.

#### Exclusion criteria

Households or individual adult members currently enrolled in any other research study on waste management /segregation.Households of volunteer and project staffHousehold whose waste mixes with waste generated from commercial use (Shops, markets, salon, school, clinics etc.,) and industrial use.

#### Definition of household and slum household

We will follow the definition of household given by Census of India i.e., A ‘household’ is usually a group of persons who normally live together and take their meals from a common kitchen unless the exigencies of work prevent any of them from doing so. There may be one member households, two member households or multi-member households [28].

We will follow the slum definition given by Census of India [28, 29] in this study. According to them, slums are categorized and defined as one of the following three types:
I.**“Notified slums** (All notified areas in a town or city notified as ‘Slum’ by State, Union Territory (UT) Administration or Local Government under any Act including a ‘Slum Act’)”II.**“Recognized slums** (All areas recognised as ‘Slum’ by State, UT Administration or Local Government, Housing and Slum Boards-not been formally notified as slum under any act)”III.**“Identified slums** (A compact area of at least 300 population or about 60-70 households of poorly built congested tenements, in unhygienic environment usually with inadequate infrastructure and lacking in proper sanitary and drinking water facilities- identified by the census of India)”

Any household located within the above mentioned areas will be considered as slum households.

##### Sample size

The sample size will be based on the differences in proportion, assuming that 50% households segregate waste in both groups. As we could not find previous literature quantifying the effect of similar kind of intervention in Indian setting, we assumed that in our study the intervention will increase the waste segregation practice in the intervention group by 20% compared to the control group. Given a 5% significance level and 80% power, then the minimum sample size is *n* = 184 per group. Assuming a design effect of 2 to adjust for the clustering effect, with 10% non-response rate and 20% loss to follow-up, the final sample size for each arm will be 425 households (total 850 households).

We have fixed the cluster number as eight. As the required sample size is 850 households, we will recruit 850 households from 8 wards i.e., around 110 households (cluster size) will be recruited from each ward.

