### Sampling strategy

The Ujjain Municipal Corporation is divided into 54 wards. Wards are the last administrative unit of the municipality. Wards will be our randomization unit (cluster).

All the wards in Ujjain Municipal Corporation (*n* = 54) will be chronologically arranged according to percentage of slum population in each ward. The consecutive wards will be arranged into pairs (*n* = 27 ward pairs). These pairs will be divided into quartiles based on the percentage of slum population. One ward pair will be selected by simple random sampling from each quartile. Thus, a total of four ward pairs (eight wards) will be selected. The lottery method (simple randomization) will be used to randomly allocate wards in each pair into intervention and control groups.

A survey team will conduct a preliminary door to door survey to list the total number of households in the selected eight wards. They will gather information of slum and non-slum households. Thus, at the end of this process, we will have a sampling frame (line listing of households classified as slum and non-slum areas).

After the household listing, each ward (cluster) will be divided into groups of 22 consecutive households. To meet the required sample size, we will identify at least five groups of 22 households from each ward (5X22 = 110 households). In total, 440 households will be recruited for the intervention group and another 440 for the control group.

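### The sample-size chain does not reproduce: 184 per group does not follow from the stated two-proportion inputs, and 425 per arm does not follow from 184 with the stated inflations

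*Protocol article*

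**What the plan says.** The Sample size section of the protocol article prints one complete calculation.

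- Type of comparison: "The sample size will be based on the differences in proportion".
- Starting rate: "assuming that 50% households segregate waste in both groups".
- Effect: "the intervention will increase the waste segregation practice in the intervention group by 20% compared to the control group". The scale (percentage points or relative) is not given.
- Error rates: "Given a 5% significance level and 80% power". Sidedness is not given.
- First result: 184 per group.
- Inflation: a design effect of 2, then "with 10% non-response rate and 20% loss to follow-up, the final sample size for each arm will be 425 households", 850 in total.

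The abstract repeats the figure: "The study will recruit 425 households in intervention and control groups". The Sampling strategy section builds recruitment from five groups of 22 households in each of eight wards: "In total, 440 households will be recruited for the intervention group and another 440 for the control group". Under Primary outcome measures, the first primary outcome is the change from baseline in the proportion of households segregating, compared between arms as a difference in differences.

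**The concern.** All inputs and both results are printed, so the calculation can be checked without an analysis plan, and two links fail. The first runs from the assumed proportions to 184. The second runs from 184 to 425, and it fails however the first is read.

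At stake is what the trial can detect. The stated 80% power cannot be attached to the stated effect by the comparison that the paragraph describes. The planned number is also smaller than the protocol's own first result requires once its own allowances are applied. A null result on the first primary outcome could not be read against this plan.

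**Working it through.** **Inputs.** From Sample size: 50% starting rate, 20% increase, 5% significance, 80% power, design effect 2, 10% non-response, 20% loss. From Sampling strategy: 440 per arm. Assumption: two-sided test, so z = 1.960 and 0.8416, and (1.960 + 0.8416)² = 7.849.

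**Step 1: can 184 be reproduced?** With p1 = 0.50 and difference d, the unpooled formula is n = 7.849 × [p1(1−p1) + p2(1−p2)] / d².

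- 20 points (p2 = 0.70): 7.849 × (0.25 + 0.21) / 0.04 = 90.3, so 91 per group.
- 20% relative (p2 = 0.60): 7.849 × (0.25 + 0.24) / 0.01 = 384.6, so 385 per group.

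| Reading | Unpooled | Pooled | Continuity-corrected |
|---|---|---|---|
| 50% vs 70% | 91 | 93 | 103 |
| 50% vs 60% | 385 | 388 | 408 |

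A one-sided test gives 74 or 305 (pooled), and 90% power two-sided gives 124 or 519. None is near 184. At 184 per group the power is 97.7% for 50% vs 70% and 48.7% for 50% vs 60%.

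Two calculations that the text does not state come close:

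- The total, not per-group, number for 50% vs 70%: 2 × 93 = 186.
- A difference in differences with four independent cells (50/50/50/70): 7.849 × (3 × 0.25 + 0.21) / 0.04 = 188.4, so 189 per group.

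**Step 2: can 425 be reproduced from 184?** 184 × 2 = 368. Then:

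| Allowance applied | Per arm |
|---|---|
| Both, ÷ (0.9 × 0.8) | 511.1 |
| Both, ÷ 0.7 | 525.7 |
| Both, × 1.1 × 1.2 | 485.8 |
| Both, × 1.3 | 478.4 |
| 10% only (× 1.1 or ÷ 0.9) | 404.8 or 408.9 |
| 20% only (× 1.2 or ÷ 0.8) | 441.6 or 460.0 |

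No variant gives 425.

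**Step 3: what the planned numbers leave, against the required 368.**

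| Recruited per arm | Both losses after recruitment (× 0.72) | Only the 20% loss after recruitment (× 0.8) |
|---|---|---|
| 425 | 306 (17% short) | 340 (8% short) |
| 440 | 317 (14% short) | 352 (4% short) |

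**Step 4: what 440 per arm gives.** Effective size after both losses and design effect 2: 440 × 0.72 / 2 = 158.4 per arm.

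- Single time point, pooled normal approximation: 95.6% power for 50% vs 70% and 43.2% for 50% vs 60%. The difference detectable with 80% power is about 15.5 points (50% vs 65.5%).
- Difference in differences of 20 points, independent cells: standard error √(0.96 / 158.4) = 0.0778; 0.20 / 0.0778 − 1.960 = 0.61; power about 73%.
- At 425 per arm (153 effective) the corresponding powers are 95%, 42% and 71%.

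**The case against.** The strongest defence concerns 184. The primary outcome is a difference in differences, and a common 50% in both groups fits a shared baseline. The four-cell formula gives 189, and at 184 its power is 79.1%, close to the stated 80%. This stands as a plausible origin. It rules out the claim that the first step was simply doubled by mistake. But the Sample size section does not name that formula, the same households are followed over time so the cells are not independent, and it does nothing for 425.

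Four stronger readings are tempting and are not supported.

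- *The trial is heavily underpowered.* This needs the relative reading of the 20%. The text speaks of differences in proportion, and 184 is less than half of the 388 which that reading requires, so percentage points are the more natural reading. On a single-time-point comparison, 20 points would need only 93 × 2 / 0.72 = 258.3, or 259 per arm.
- *The trial is therefore comfortably powered.* That figure, and the 96%, belong to a single-time-point comparison. For the stated difference in differences, independent cells give about 73%. Within-household correlation would raise this, but the document gives no value.
- *850 and 880 contradict each other.* Sampling strategy explains 880 as rounding up to whole groups of 22 to meet the requirement. The products 2 × 425 = 850 and 4 × 5 × 22 = 440 are correct. Only the wording is loose.
- *425 reveals a hidden 65% assumption.* It is true that 170 × 2 / 0.8 = 425, and 170 is the pooled n for 50% vs 65%. No such effect appears in the document, so this is conjecture.

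That an article condenses the full protocol does not help: the steps are printed here, and they disagree.

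**Conclusion.** The concern holds for both links. The step from 184 to 425 is wrong on every combination of the stated allowances tried, and this does not depend on how the effect is read. The step to 184 does not follow from the comparison described, on either scale of the 20%. The formula that would come closest to it is not stated.

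Measured against the protocol's own requirement of 368 analysable households per arm, the plan is 4–17% short. The low end takes 440 recruited with non-response before recruitment; the high end takes 425 with both losses afterwards.

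These results assume a two-sided test, normal approximations and the stated design effect of 2. Whether that design effect suits eight wards of about 110 households was not tested here. The documents do not settle whether the trial is too small or larger than needed, because they fix neither the scale of the effect nor the formula. A printed figure on which the trial relies is wrong as written, and it should be corrected.

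**What to change.** Keep the planned 880 households (440 per arm) and rewrite the Sample size paragraph:

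1. State the effect as two proportions, on an explicit absolute or relative scale.
2. Name the formula and sidedness: single time point or difference in differences, the latter with any within-household correlation assumed.
3. Multiply by the design effect, then divide by (1 − 0.10) and (1 − 0.20), saying whether non-response falls before or after recruitment.
4. Restate the power or detectable difference that 440 per arm gives. If design effect 2 and both losses are kept, the Step 4 figures apply.
5. As a minor point, once the chain is corrected, describe the calculated number (now 850) as the requirement and 880 as the recruitment target after rounding to groups of 22, in the abstract as well.

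The cost is one paragraph and a line of the abstract. The downside is that the stated power or detectable effect may look less favourable.

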### Sampling strategy

The Ujjain Municipal Corporation is divided into 54 wards. Wards are the last administrative unit of the municipality. Wards will be our randomization unit (cluster).

All the wards in Ujjain Municipal Corporation (*n* = 54) will be chronologically arranged according to percentage of slum population in each ward. The consecutive wards will be arranged into pairs (*n* = 27 ward pairs). These pairs will be divided into quartiles based on the percentage of slum population. One ward pair will be selected by simple random sampling from each quartile. Thus, a total of four ward pairs (eight wards) will be selected. The lottery method (simple randomization) will be used to randomly allocate wards in each pair into intervention and control groups.

A survey team will conduct a preliminary door to door survey to list the total number of households in the selected eight wards. They will gather information of slum and non-slum households. Thus, at the end of this process, we will have a sampling frame (line listing of households classified as slum and non-slum areas).

After the household listing, each ward (cluster) will be divided into groups of 22 consecutive households. To meet the required sample size, we will identify at least five groups of 22 households from each ward (5X22 = 110 households). In total, 440 households will be recruited for the intervention group and another 440 for the control group.

### Intervention details

#### Intervention group

The intervention will be at household level. Households selected for the intervention arm will be visited fortnightly by a volunteer who will give improved waste segregation information. This intervention will be in addition to the routine /general information on waste segregation that is given by the municipality.

The volunteer will be an adult individual recruited from the same cluster (ward) as their households (permanent resident of the locality) able to read and write the local language, with interest and willingness to spend time to improve waste management in their residential area. The intervention will be delivered primarily through one to one interactive sessions. The interaction will be in the local language supported by flip cards, pictures, and visuals. The volunteer will visit fortnightly for 12 months, meaning that a volunteer will visit a household at least 24 times during the intervention period. The total duration of each interaction session will be about 15–30 min. At least primary and/or secondary members of households responsible for waste disposal identified in the baseline survey by self-reported method must be available in these interactive sessions. However, all other available and interested adult members will be included in the sessions. Attendance of presenting members and any other information shared by household members will be systematically recorded by the volunteer in a logbook. The broad topics to be covered in the improved information include types of waste, correct waste segregation methods, residents’ role and responsibilities, waste management and its effects on health and wellbeing. Standard operating procedure (SOPs) will be prepared, so that the intervention package will be standard in all intervention households to avoid the risk of intervention variability and to increase intervention fidelity. One volunteer will be allocated to approximately 22 households. The volunteer will be paid small monetary incentive for their role in the project. At least two induction training programmes will be organized for volunteers to train the volunteers in all aspects of intervention content and SOPs to ensure that the intervention is delivered uniformly across households. They will be also trained in communication skills. Two refresher trainings are planned during the intervention period (4th month and 8th month).

